## Data collection, management and analyses

### Outcome data collection

CHWs collect child anthropomorphic measures and parent self-report data from participants at three time points: baseline, 3 months (1 month post-intervention) and 6 months (4 months post-intervention). CHWs collect child anthropomorphic measures with a portable stadiometer and scale. Measurements for both weight and height are taken twice. If the two measurements differ by more than 0.5 cm for height and 0.5 lbs. for weight, a third measurement is taken. The final measurement is the average of the two measurements that coincide most.

The questionnaires on family behavior and child nutrition and physical activity is administered by trained CHWs using REDCap [37]. The information is either collected on iPads or on printed copies of the questionnaire and transcribed later.

### Qualitative data collection

The LVB evaluation uses mixed methods, with qualitative data complementing quantitative outcomes to contextualize the results. The CHWs conduct focus groups with a sample of the parent participants immediately after the intervention, 1 month after the intervention or 4 months after the intervention. The focus groups correspond with the post and follow-up data collection time points. The focus group explores process-oriented themes to help the LVB team understand barriers to attendance, and support recruitment efforts. The focus groups also explore themes of motivation, making and maintaining healthy family behavior changes, and the physical activity and nutrition environment in the intervention community.

While the parents complete the focus group, the children participants also take part in guided evaluation activities. The activities are modeled after the interactive and playful format of the class, with age-appropriate games and drawings. The guided activities explore the children’s perceptions of health and what they learned from the class. The teen health facilitators, aided by a CHW or the university evaluator observer, facilitate the guided activities with children.

### Data management

REDCap is a secure web application supported by the University of Arizona that allows online data entry and management [37]. REDCap complies with the Health Insurance Portability and Accountability Act (HIPAA) security guidelines and is approved and endorsed by the University of Arizona Privacy Office and the Institutional Review Board (IRB).

The LVB coordinator or evaluator check the REDCap data after each data collection to verify accuracy and quickly correct any potential issues. There are also quality control measures built into REDCap, which display the height and weight from the previous data collection point for the post and follow-up measurements so that the CHWs can easily check the measurements for errors. In the event that the LVB team is unsure about the accuracy of child anthropomorphic measurements, the CHWs will seek written consent from participants to check the values against height and weight measurements recorded in the FQHC’s Electronic Health Record around the same time period.

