#### Justification for study comparators and design

The study population includes patients from two of the FQHC’s four clinics: the comparison group is drawn from patients in a satellite clinic 10 miles from the intervention community. The patient populations of the two communities are demographically similar. After outcome data collection is complete, the comparison group will have the opportunity to participate in the full intervention.

Our rationale for a quasi-experimental study design takes into account the realities of an FQHC in a rural setting. Randomization would be awkward with a project in which pediatricians are referring their patients, and it would be uncomfortable for CHWs and medical staff to explain and justify random assignment to parents. Group-based randomization was not possible because the FQHC has too few clinics. The use of a comparison group from a different clinic site with a similar demographic profile is a practice-based research design that affords key evidence for other FQHCs that wish to adopt and evaluate the intervention [30].

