##### La Vida Buena intervention

The LVB team includes two CHWs, a CHW coordinator, a health promotion manager at the FQHC, two evaluators based out of a nearby university, and two adolescent peer educators. The La Vida Buena intervention, delivered by teams of adult Community Health Workers (CHWs) and adolescent peer health educators (Teen Health Facilitators), takes place once a week for 8 weeks. Each weekly hour-long session includes 20 min of interactive learning topics, 20 min of physical activity and 10 min of healthy food preparation and discussion. All activities are designed to encourage active learning from both the parents and the children. The interactive learning topics focus on nutrition, physical activity and healthy family habits. Teen health facilitators lead the physical activity portion of the class. The objectives of each class session and selected activities are listed in Table 1.

**Table 1 Tab1:** La Vida Buena curriculum session objectives

Session Name	Objectives	Example activities, incentives and food demonstrations
Session 1: Orientation	• Identify the program goals: Increase fruit and vegetable consumption; Increase non-school physical activity; Reduce sugary drink intake and other refined carbohydrates • Identify two health issues related to being overweight • Recognize La Vida Buena as an informative and fun program	• Physical activity through play • Incentive: jump ropes • Food demo: fruit salad
Session 2: Gotta Love those Fruits and Veggies	• Name GO FOODS - to eat almost anytime (Fruits and veggies) • Identify SLOW FOODS - to eat less often (Grains, dairy, protein) • Name WHOA FOODS - to eat once in a while (High caloric, high fat foods) • Express one strategy to eat in a more healthy manner	• Go/Slow/Whoa traffic light game • Incentive: fruit/veggie stuffed animals and measuring cups • Food demo: DIY salad bar
Session 3: Guess what’s in the bowl	• Understand what a serving size is • Understand MyPlate	• Guess how much is in the cereal bowl • Incentive: MyPlate plate, smoothie cup • Food demo: cauliflower rice
Session 4: Breakfast for your Brain	• Identify breakfast as the most important meal of the day • Identify a healthy cereal by label reading based on fiber and sugar contents • Write one healthy breakfast menu as a family	• Label detective with magnifying glasses • Incentive: balls and Tupperware set • Food demo: apple “cookies”

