#### Comparison group

The comparison group is drawn from a satellite clinic in a neighboring community. The characteristics of the pediatric population are similar in both clinics. CHWs deliver a 50-min educational session either one-on-one or in a group setting. The educational session includes 40 min of interactive learning activities focused on nutrition and 10 min of physical activity information, and focuses on some of the basic strategies and key messages covered in the 8-week La Vida Buena intervention. The CHW facilitator discusses nutrition and physical activity strategies with the parent and child in a single educational session, but the session is more didactic and does not include a physical activity session. The session objectives for the comparison group are listed in Table 2.

**Table 2 Tab2:** Learning Objectives for Comparison Group Single Educational Session

Session	Objectives
Comparison Group Education Session	By the end of the session participants will be able to: • Identify Go foods - to eat almost anytime (Fruits and Veggies) • Identify Slow foods - to eat sometimes (Grains, Dairy, Protein) • Identify Whoa foods - to eat once in a while (High caloric, High fat foods) • Identify the recommended daily fruit and vegetables portions

The FQHC will offer the full LVB intervention to participants in the comparison group following the completion of data collection.

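### Height and weight for the primary BMI z-score are taken by CHWs who know the arm; REDCap shows them the child's previous values, with no stated safeguard that the new readings are entered first

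*Protocol article*

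**What the plan says.** All references are to the Protocol article.

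- **Who delivers.** Under La Vida Buena intervention, the programme is "delivered by teams of adult Community Health Workers (CHWs) and adolescent peer health educators". Under Comparison group, "CHWs deliver a 50-min educational session either one-on-one or in a group setting". The staffing is small: "The LVB team includes two CHWs, a CHW coordinator, a health promotion manager at the FQHC", plus two university evaluators and two adolescent peer educators.
- **How arms are formed.** Under Justification for study comparators and design, "the comparison group is drawn from patients in a satellite clinic 10 miles from the intervention community". Arm therefore follows from site.
- **Who measures.** Under Outcome data collection, "CHWs collect child anthropomorphic measures with a portable stadiometer and scale", at baseline, 3 months and 6 months. Height and weight are each taken twice. A third reading follows if the two differ by more than 0.5 cm or 0.5 lb, and the closest pair is averaged.
- **What they see.** Under Data management, the built-in REDCap controls "display the height and weight from the previous data collection point for the post and follow-up measurements", to help CHWs detect errors.
- **What is re-checked.** The same section provides for comparison with the health record, subject to written consent: "In the event that the LVB team is unsure about the accuracy of child anthropomorphic measurements". The coordinator or evaluator also reviews the data after each collection and corrects problems.

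The primary outcome is change in BMI z-score from baseline to 6 months, analysed by ANCOVA with the baseline value as the only covariate.

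**The concern.** Two features of the measurement procedure act directly on the primary outcome.

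The first is anchoring. A measurer who can see the last height and weight may read the stadiometer or scale closer to those values, or may repeat a reading that looks surprising until it fits. If this happens equally in both arms, it shrinks measured change and dilutes any true difference.

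The second is selective correction. People who know the arm, and can see which way a value has moved, judge whether that value is doubtful. If doubt arises more readily for unwelcome changes in one arm, the between-arm difference is biased.

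Baseline adjustment cannot remove follow-up measurement error that differs by arm. Because allocation is by clinic, there is also no point at which the measurer could plausibly be unaware of the arm. The article describes no masked or independent assessor.

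**Working it through.** **1. The plan's own figure.** Inputs from Sample size: difference 0.2, SD 0.4, type 1 error 5%, power 80%, attrition 25%, 100 per site. Two assumptions are needed: the test is two-sided (the article does not say), and 0.4 is the per-child SD entering the group comparison.

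- n per arm = 2 × (1.96 + 0.842)² × 0.4² / 0.2² = 62.8, so 63.
- With attrition: 63 / (1 − 0.25) = 84 per arm, 168 in total.

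The stated 200 is larger than this. It came from simulations whose settings are not given, so I do not call it an error, and nothing below depends on it. With 100 per arm and 25% lost, 75 per arm remain.

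**2. What the duplicate rule can detect.** Write the two readings at one visit as r₁ = true value + b + e₁ and r₂ = true value + b + e₂, where b is any shift toward the displayed value and the e terms are random reading errors. The rule acts on r₁ − r₂ = e₁ − e₂. The shift b cancels, so the 0.5 cm and 0.5 lb limits control random disagreement but cannot see b. Averaging the closest pair leaves b intact.

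**3. When the display appears.** The article says that previous values are displayed and why. It does not say whether they appear before or after the new readings are entered. The stated purpose fits either order, so protection against anchoring is not established.

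**4. Which values get a second look.** The 0.5 cm and 0.5 lb limits apply only within a visit. For comparison with the previous visit and with the health record, the trigger described is the team's own uncertainty. The text does not say which value stands after a health-record check.

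**5. How sensitive the test is to a between-arm bias (illustration).** The bias sizes are assumptions; none comes from the article.

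- Standard error at 75 per arm = 0.4 × √(2/75) = 0.0653 BMI z.
- False-positive rate under no true effect with bias B = 1 − Φ(1.96 − B/SE) + Φ(−1.96 − B/SE).

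| Assumed between-arm bias (BMI z) | B/SE | Two-sided false-positive rate |
|---|---|---|
| 0 | 0 | 5.0% |
| 0.02 | 0.31 | 6.1% |
| 0.05 | 0.77 | 11.9% |
| 0.10 | 1.53 | 33.4% |

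A bias of 0.05 is one quarter of the 0.2 target difference (0.05 / 0.2 = 0.25).

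**The case against.** The defence has several sound points.

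- **Anchoring alone is probably common to both arms.** One REDCap check serves both sites and CHWs deliver both arms. Common anchoring pulls the estimate toward zero; it does not manufacture benefit. Inflation needs the further step of selective re-checking, which the article makes possible but does not show. This stands.
- **The health-record check is not in the CHWs' hands alone.** The article gives the trigger to the LVB team, which includes the coordinator and the university evaluators. The CHWs' stated part is to seek consent. This stands.
- **There is an objective replicate rule.** It deserves credit for limiting random error within a visit, but it does not address the displayed value.
- **Discrepancy limits and query rules often sit in a data-management manual.** That is fair, and the absence of such detail from an article is not the point. The display of previous values and the use of delivering staff as assessors are stated choices.

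A reader might infer more than the text supports:

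- *That anchoring costs the trial power.* If each reading is pulled 10% back toward the earlier value, the mean difference falls to 0.18, but the SD of change falls to 0.36. Then 0.18 / 0.36 = 0.50, the same as 0.2 / 0.4. Power drops only if the mean shrinks and the spread does not, and nothing in the article suggests that. The estimate would still be diluted.
- *That a height error in one child can be set against the 0.2 target.* The target is a difference between arm means. Matching it would need the same systematic error throughout one arm and none in the other.
- *That the same CHW teaches and measures a given child.* With two CHWs this is likely, but it is not stated.

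**Conclusion.** The point holds as a weakness in procedure, not as a demonstrated bias. The documents establish that CHWs deliver both arms, can tell the arm from the site, measure the primary outcome, and are shown earlier values at the later visits. That they are unmasked is inferred from delivery and site; the article does not use the word. The replicate rule does not close the gap.

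Neither the direction nor the size of any bias can be derived. The illustrative rise in the false-positive rate to about 12% rests on an assumed 0.05 BMI z between-arm bias, 75 completers per arm, an SD of 0.4 and a two-sided 5% test. It shows that a modest differential error would matter, not that one is expected. Because the risk falls on the primary outcome of an unrandomised comparison and is cheap to remove, the change is worth making.

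**What to change.** In Data management:

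1. State that REDCap shows the previous height and weight only after both new readings have been entered and locked.
2. Then apply one pre-set numeric discrepancy limit, in both directions and identically in both arms, as the trigger for a repeat reading or a health-record check.
3. Retain the values as first entered alongside any corrected ones, and report a sensitivity analysis of the primary outcome on the uncorrected values.

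This keeps the error check the team wants. The cost is a small REDCap change and a few more repeat readings. It alters no stated sample size, endpoint or primary model.

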### Outcomes

#### Primary outcomes

The primary outcome is the change in BMI z-score between baseline and 6 months follow up among subjects participating in the program La Vida Buena as compared with those receiving a single educational class.

#### Secondary outcomes

Secondary outcomes include difference in family-focused healthy lifestyle practices, difference in fruit and vegetable consumption, difference in the consumption of sugary drinks and beverages and other refined carbohydrates, and difference in non-school weekly physical activity between baseline and follow-up. Secondary outcomes are measured through parent self-report using the Family Nutrition and Physical Activity (FNPA) Tool and the International Physical Activity Questionnaire (IPAQ). The FNPA has been validated as a tool to capture important elements of the family environment that relate to risk for child overweight and increasing BMI [38, 39]. The International Physical Activity Questionnaire also has demonstrated validity and reliability in various settings [40]. The outcome of physical activity will be converted to youth metabolic equivalents (MET_y_ youth) units using the Youth Compendium of Physical Activity (YCPA) compiled by the National Collaborative on Childhood Obesity Research [41]. This compendium provides MET estimates for common physical activities stratified by sex and age group. The questions regarding vigorous physical activity include as examples soccer, running, and swimming. The questions regarding moderate physical activity include as example walking, skating, and paddling in a pool. The YCPA includes all these activities except skating, but rollerblading is included and can be used as a substitute for skating. Using the indicated activity, duration of the activity, and basal metabolic rate (BMR) as calculated by the Schofield equations an estimate of MET_y_ can be obtained for each participant. Note that the Schofield equations for BMR are included in the YCPA. Fruit and vegetable consumption and sugary drink consumption outcomes will be measured in units of “servings per week”.

### Statistical methods

We will summarize all baseline continuous variables using descriptive statistics, i.e. mean and standard deviation, stratified by treatment group. We will summarize categorical variables using frequencies and percentages. Baseline clinical and demographic data will be compared between the intervention and wait-list control groups. Dichotomous and ordinal variables will be examined using either chi-square test or Fishers exact test and continuous measures with two-sample t-test or two sample non-parametric Wilcoxon Rank Sum Test. Feasibility outcomes (recruitment, retention, etc.), will be described using frequencies/percentages, and 95% confidence intervals.

#### Primary analysis

The primary endpoint will be change BMI z-score from baseline to 6 months follow up among subjects participating in the program La Vida Buena compared to those receiving an educational class. BMI z-scores will be modeled using an analysis of covariance (ANCOVA) model. Let BMI_*ijk*_ represent the BMI z-score for the *j*^*th*^ subject in the *i*^*th*^ treatment group at the *k*^*th*^ time point for *k* ∈ {0, 1, 2}. The *k* levels for time point correspond to baseline (k = 0), 3 months follow up (k = 1), and 6 months follow up (k = 2). The ANCOVA model is specified as,$$ {\mathrm{BMI}}_{ij2}={\mathrm{BMI}}_{ij0}+{T}_i+{\epsilon}_{ij2} $$where *T*_*i*_ is the intervention effect for and *ϵ*_*ij*2_ is the error term. The effect *T*_*i*_ will be tested at the *α* = 0.05 significance level and the effect size along with a 95% confidence interval will be reported.

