### Research design and setting

#### Trial design

This is a parallel two-arm quasi-experimental behavioral trial based in two communities.

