#### Secondary analysis

Secondary outcomes of [1] family practices, [2] physical activity, [3] consumption of fruits and vegetables, and [4] consumption of sugary drinks and other refined carbohydrates will be analyzed in a using ANCOVA models as specified for the primary outcome, i.e. secondary outcome measure at 6 months follow up is the response, intervention group is the factor to be tested, and an adjustment is made for baseline value of the outcome.

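### The arms are two non-randomised clinics, yet the primary and secondary models adjust only for the baseline value of the outcome, leaving out baseline predictors the protocol already measures.

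*Protocol article*

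**What the plan says.** Under Trial design: "This is a parallel two-arm quasi-experimental behavioral trial based in two communities". Under Justification for study comparators and design, the arms are one clinic each: "the comparison group is drawn from patients in a satellite clinic 10 miles from the intervention community". The same section explains the lack of randomisation: "Group-based randomization was not possible because the FQHC has too few clinics". It supports comparability with a sentence that carries no figures: "The patient populations of the two communities are demographically similar". The Comparison group section says much the same of the two pediatric populations, again without figures.

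Under Primary analysis: "BMI z-scores will be modeled using an analysis of covariance (ANCOVA) model". The equation is introduced by "The ANCOVA model is specified as" and has three terms on the right: baseline BMI z-score, a treatment term that the text calls the intervention effect, and error. Under Secondary analysis the models follow the primary one, and "an adjustment is made for baseline value of the outcome".

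Under Statistical methods: "Baseline clinical and demographic data will be compared between the intervention and wait-list control groups". The comparisons use chi-square, Fisher, t or Wilcoxon tests. The text gives their results no role in the outcome models.

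The Outcomes section describes the FNPA as validated for aspects of the family environment related to a child's overweight risk and rising BMI. Outcome data collection and Informed consent show that parent-reported nutrition and activity data are gathered at baseline.

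**The concern.** An ANCOVA on the baseline outcome alone suits a randomised trial, where other prognostic factors are balanced in expectation. Here nothing balances them. Families enter through referral and invitation at two different clinics. They are also asked to commit to different things, eight weekly sessions or one 50-minute session, so the families who agree may differ even if the clinic populations are alike. The similarity statements concern clinic populations, not enrolled families.

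If enrolled families differ in habits that drive BMI z-score over the next six months, that difference enters the treatment term and its 95% confidence interval. It could mimic a benefit or hide one. The protocol itself treats the family environment as related to rising BMI and measures it at baseline, yet leaves it out of the primary model.

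This is not a detail that a condensed article leaves to a fuller plan, because the article writes the primary model out.

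**Working it through.** **Inputs from the protocol (Sample size).** Target difference 0.2 BMI z units; SD 0.4; type 1 error 5%, taken as two-sided because a 95% confidence interval is reported; 100 per arm; 25% attrition, so 100 × 0.75 = 75 completers per arm; power 80%.

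**The plan's own figure.** n per arm = 2 × (1.960 + 0.842)² × 0.4² / 0.2² = 62.8, so 63. Allowing for attrition, 63 / 0.75 = 84 per arm, 168 in all. The stated 200 is larger than these inputs need, and 75 completers per arm give about 86% power. An SD of about 0.437 would give 80% at 75 per arm. The point below does not depend on this gap.

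**Precision of the treatment term.** SE = 0.4 × √(2/75) = 0.0653. An observed difference of about 1.96 × 0.0653 = 0.128 is significant.

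**Effect of a residual between-clinic shift b, with no intervention effect.** P(reject) = Φ(−1.96 + b/SE) + Φ(−1.96 − b/SE). Every b is an assumption.

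| Assumed b (BMI z) | b/SE | P(reject) |
|---|---|---|
| 0 | 0 | 5.0% |
| 0.03 | 0.46 | 7.4% |
| 0.05 | 0.77 | 11.9% |
| 0.10 | 1.53 | 33.4% |

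**What adjustment can recover.** A simulation of the stated ANCOVA (4,000 runs, 75 per arm, no intervention effect) added one covariate that is independent of baseline BMI z-score and differs by 0.5 SD between clinics. Both settings are assumed.

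| 1 SD of the covariate moves 6-month BMI z by | Bias, stated model | False positives, stated model | Bias, covariate added | False positives, covariate added |
|---|---|---|---|---|
| 0.1 | 0.050 | 11.7% | 0.000 | 5.3% |
| 0.2 | 0.101 | 33.1% | 0.001 | 4.9% |

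**Why the association must be conditional on baseline.** Suppose instead that a factor correlates 0.3 with both baseline and 6-month BMI z-score, differs by 0.4 SD between clinics, and 0.4 is the SD of change. Its standardised coefficient given baseline is (0.3 − 0.3ρ)/(1 − 0.3²), where ρ is the baseline-to-6-month correlation.

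- ρ = 0.8: coefficient 0.066. Outcome SD = 0.4/√(2 × 0.2) = 0.632. Bias = 0.4 × 0.066 × 0.632 = 0.017.
- ρ = 0.9: coefficient 0.033. Outcome SD = 0.4/√(2 × 0.1) = 0.894. Bias = 0.4 × 0.033 × 0.894 = 0.012.

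If the imbalance also shifts mean baseline BMI z-score by 0.3 × 0.4 = 0.12 SD, the imbalance left after adjustment is 0.4 − 0.3 × 0.12 = 0.364 SD, and the biases become 0.015 and 0.011. Across 0.011 to 0.017 the rejection rate is between 5% and 6%. A factor that acts mainly on the level of BMI z-score is thus largely handled by the stated model. A factor that acts on its change is not.

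**The case against.** The protocol is open about its design and gives practical reasons for it. Eligibility narrows case mix: one FQHC, age 5–8, BMI above the 85th percentile, Spanish-speaking parent and child. Baseline BMI z-score is a strong covariate, and the z-score already standardises for age and sex to a large extent. Summaries by arm would make an imbalance visible, and the baseline tests are not blind to one: with 100 per arm, a 0.4 SD difference is detected with about 80% power. A fuller analysis plan may hold adjusted sensitivity analyses.

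Much of this stands, and it rules out several stronger readings that a reader might infer.

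- That every difference between the clinics' families is reported as an intervention effect. Only what predicts 6-month BMI z-score beyond baseline does so.
- That a factor correlated 0.3 with the outcome and imbalanced by 0.4 SD gives a bias of 0.3 × 0.4 × 0.4 = 0.048. That product uses the marginal association. The conditional one, under the assumptions above, gives 0.011 to 0.017.
- That the article excludes any adjusted analysis. It is silent on supportive analyses.
- That socioeconomic position or season of enrolment is a known confounder here. The documents do not list household socioeconomic items, and nothing says that the arms enrol in different seasons.

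What the objection does not answer is that the primary model itself is fixed without measured predictors. Making an imbalance visible does not remove it from the estimate, and covariates added after the baseline tables have been seen would be chosen from the data.

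**Conclusion.** The point holds in this form: the stated primary and secondary models adjust only for the baseline outcome in a comparison of two non-randomised clinics, and the treatment term is called the intervention effect without qualification. Differences between enrolled families that predict 6-month BMI z-score beyond its baseline would bias that term, although likely predictors are measured at baseline.

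The actual size is unknown. The rates of about 7%, 12% and 33% are correct arithmetic for hypothetical residual shifts of 0.03, 0.05 and 0.10, given SD 0.4, 75 completers per arm and a two-sided 5% test. They are not estimates of what this trial will show.

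A reader might also infer that adjustment would make the estimate a clean measure of effectiveness. It would not. With one clinic per arm, clinic and community are fully aliased with the intervention, and no covariate set separates them.

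**What to change.** Make the primary model an ANCOVA of 6-month BMI z-score on treatment and a short covariate set fixed in advance: baseline BMI z-score, baseline FNPA score, baseline physical activity, child age and sex, and whichever demographic items the study actually holds, named in the plan. Enter them whatever the baseline tests show. FNPA and physical activity carry most of the argument, since the z-score already largely accounts for age and sex.

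Use the same approach for each secondary outcome, with its own baseline value in the set. Keep the present model as a supportive analysis. Standardised differences in place of baseline tests, and a propensity-weighted sensitivity analysis, are reasonable options but not required.

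State in the plan and the report that residual clinic or community effects cannot be separated from the intervention.

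The cost is a revision of the analysis text and a few degrees of freedom out of about 150 completers. No new participants or visits are needed, provided the set is confined to items already collected.

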## Methods: recruitment

### Sample size

To detect a minimal important difference of 0.2 BMI z-standardized units between baseline and 6-month follow-up, an estimated sample size of *n* = 200 participants is required. This calculation assumes 100 participants for the intervention site and 100 participants for the comparison site, with a 25% attrition rate, in order to achieve 80% power. The power calculation was completed using ANCOVA simulations with a type 1 error rate of 5% and a standard deviation in group differences of 0.4 BMI z standardized units.

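### The primary model is called ANCOVA, but its printed equation gives baseline no coefficient, so read literally it is a change-score comparison

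*Protocol article*

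**What the plan says.** All references are to the protocol article; a separate analysis plan is not at hand.

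- **Primary analysis, endpoint and method.** "The primary endpoint will be change BMI z-score from baseline to 6 months follow up", and "BMI z-scores will be modeled using an analysis of covariance (ANCOVA) model".
- **Primary analysis, equation.** The model is then printed as "BMI}}_{ij2}={\mathrm{BMI}}_{ij0}+{T}_i+{\epsilon}_{ij2". In plain notation: BMI_ij2 = BMI_ij0 + T_i + e_ij2, where 0 is baseline and 2 is 6 months.
- **Primary analysis, group term.** T "is the intervention effect for and" the error term follows. The definition breaks off in the text at hand, perhaps through conversion, and gives no reference level or constraint. T is tested at the 0.05 "significance level and the effect size along with a 95% confidence interval will be reported".
- **Sample size.** Power came from "ANCOVA simulations with a type 1 error rate of 5% and a standard deviation in group differences of 0.4 BMI z standardized units".
- **Secondary analysis.** Four further outcomes are analysed "using ANCOVA models as specified for the primary outcome". This is spelled out as the 6-month value as response, group as factor, and "an adjustment is made for baseline value of the outcome".
- **Trial design.** The groups are two communities served by different clinics, without randomisation.

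**The concern.** ANCOVA estimates the slope of follow-up on baseline from the data. The printed equation has no slope to estimate. Programmed as printed, it makes no fitted adjustment for baseline, and the same specification is passed on to the parent-reported secondary outcomes.

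In a randomised trial both models target the same effect, and the choice mainly affects precision. Here the sites may differ at baseline. The two models then answer somewhat different questions and can return different estimates. The formal specification of the primary analysis should not leave that open.

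**Working it through.** **1. The plan's own figure.** Inputs from Sample size: difference 0.2, SD 0.4, 5% type 1 error (taken as two-sided), 80% power, 25% attrition, 100 per site. The usual two-mean formula gives 2 × (1.96 + 0.84)² × 0.4² / 0.2² ≈ 63 evaluable per arm. Then 63 / 0.75 = 84 per arm, or 168 in total, against the stated 200. With 75 evaluable per arm (100 × 0.75), power is about 86%, against the stated 80%. The 200 is therefore not reproduced, but it exceeds what these inputs need, and the correlation used in the simulations is not given. The present point does not depend on it.

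**2. The equation.** Subtract BMI_ij0 from both sides:

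BMI_ij2 − BMI_ij0 = T_i + e_ij2.

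This is a model for change with the baseline slope fixed at 1. The model described in Secondary analysis is BMI_ij2 = mu + beta × BMI_ij0 + T_i + e_ij2 with beta estimated. They coincide only if beta = 1.

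**3. How far the estimates differ.** Let D be the baseline mean difference between sites (intervention minus comparison).

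- Change score: (difference in 6-month means) − D
- ANCOVA: (difference in 6-month means) − beta × D
- Change score minus ANCOVA: −(1 − beta) × D

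With equal variances at both visits, beta equals the correlation rho, so the gap is (1 − rho) × D in size.

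**4. Precision.** With common variance s², the residual variance is 2s²(1 − rho) for the change score and s²(1 − rho²) for ANCOVA. The ratio is 2/(1 + rho).

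**5. Numbers.** The article gives neither rho nor D, so the range is assumed. Power is for 75 per arm and a difference of 0.2. The article does not say whether its SD of 0.4 is the ANCOVA residual SD or the SD of change, so both readings are shown. Under the first, the SD of change is 0.4 × √(2/(1 + rho)) and ANCOVA has 86% power. Under the second, the ANCOVA residual SD is 0.4 × √((1 + rho)/2) and the change score has 86%.

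| Assumed rho | Gap as a share of D | Variance ratio | Change-score power, if 0.4 is the ANCOVA residual SD | ANCOVA power, if 0.4 is the SD of change |
|---|---|---|---|---|
| 0.9 | 0.1 | 1.05 | 84% | 88% |
| 0.7 | 0.3 | 1.18 | 80% | 91% |
| 0.5 | 0.5 | 1.33 | 75% | 94% |

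For an assumed D of 0.2 z units, the gap is 0.02, 0.06 or 0.10 z, which is 10%, 30% or 50% of the 0.2 difference that the trial is sized on.

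**6. Simulation check of step 3.** Assumed: 75 per arm, 3,000 runs, baseline SD 0.5, residual SD 0.4, D = 0.2, no true effect, data generated with a slope below 1. At slope 0.8 the change score averaged −0.04 and rejected in 8.9% of runs; at slope 0.7 it averaged −0.06 and rejected in 14.6%. These match −(1 − 0.8) × 0.2 and −(1 − 0.7) × 0.2. ANCOVA averaged zero and rejected in 4.2% and 4.8%, as it must when the data are generated from its own model. The run confirms the size of the gap. It does not show which model is right for these two communities.

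**The case against.** **The equation may be shorthand.** The prose names ANCOVA in Primary analysis and in Sample size, and Secondary analysis describes adjustment for baseline as part of the same specification. An endpoint worded as change does not contradict this: with baseline as covariate, ANCOVA gives the same T whether the response is the 6-month value or the change. This objection largely stands. A reader might infer that a change-score analysis is planned, or that two rival primary models are being held open. The documents do not support that. What remains is that the section defines subscripts, time points and an error term formally, yet defines no slope anywhere, so the printed model contradicts its own label.

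**The missing intercept.** A reader might infer that leaving it out biases the effect. That holds only if T is set to 0 in the comparison group with no intercept: a common change of −0.1 in both arms would then be credited to treatment (estimate −0.10, 53% rejection under the values in step 6, but with slope 0.8 and D = 0). The article states no such constraint. If T_i is a separate mean for each group, it absorbs the intercept and the difference between the two T values is the contrast. The intercept is worth printing, but its absence is not the error.

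**Neither model is the truth.** It is tempting to call the change-score result spurious. Without randomisation that is not warranted. If the communities differ stably and would change in parallel, the change score is unbiased and ANCOVA is off by (1 − rho) × D. This objection stands in full.

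**The effect on BMI z may be small.** At rho 0.9 the gap is a tenth of the imbalance and the variance cost is 5%. The article also describes the two clinic populations as similar. This stands if the correlation is that high. The larger figures belong to lower correlations, which are more plausible for parent-reported outcomes but are assumed throughout.

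**Conclusion.** The concern holds as an error of specification. The printed primary model fixes the baseline slope at 1, and this contradicts the ANCOVA that the article names for the primary analysis and the power calculation, and the baseline adjustment that it describes when it extends the specification to the secondary outcomes.

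Its size depends on quantities that the article does not give. Under equal variances and assumed rho from 0.9 to 0.5, the two models differ by 0.1 to 0.5 of the baseline imbalance, and the change score carries 5% to 33% more residual variance. At the high end of rho the consequence for BMI z is modest.

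A reader might also infer that the trial is underpowered. The documents do not show that: only when 0.4 is read as the ANCOVA residual SD, and rho is below about 0.7, does the literal model fall short of 80% at 75 per arm. The case for correction is that the design is not randomised, the model choice can move the estimate, and the formal statement of the primary analysis should agree with its description.

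**What to change.** Replace the equation in Primary analysis with

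BMI_ij2 = mu + beta × BMI_ij0 + T_i + e_ij2,

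with beta estimated from the data and T_i set to 0 in the comparison group, so that T is the between-group contrast to be tested and reported. Complete the definition of T accordingly. State that this form is the primary analysis and that each secondary outcome uses it with its own baseline value. Any separate analysis plan should carry the same equation.

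A change-score comparison as a sensitivity analysis is optional, and reasonable given the non-randomised design. No further covariates are needed to correct this error.

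The cost is about one line of text, with no change to data collection or sample size.
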